### Sample size

2.4

The frequency of acute exacerbations is the primary outcome. According to the data in previous studies, the annual frequency of acute exacerbations in the control group was 1.08 episodes (27), and the experimental group is expected to have a 40% reduction (28), i.e., 0.648 episodes. The test level (*α*) and power (1 − *β*) of the hypothesis test were set at 0.05 and 0.9, and the sample size ratio of the experimental group and control group was 1:1. The estimated sample size for each group was 359 participants using PASS software. After accounting for a 15% dropout rate, the required sample size per group was adjusted to 423 participants. Due to the centralized blocked randomization with block sizes of 4, the sample size per group was adjusted to 424 participants. A total of 848 subjects will be enrolled in this trial.

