### Statistical analysis

2.9

SPSS software (Version 25.0) will be used for statistical analysis in this study. The study data will be analyzed according to the ITT principle, where all randomized participants will be included in the analysis according to their original group assignment, regardless of protocol deviations or different follow-up durations. For participants with varying follow-up durations, mixed-effects models for repeated measures will incorporate time as a covariate to utilize available data. Missing data will be handled using mixed-effects models for repeated measures as the primary method, with multiple imputation conducted as a sensitivity analysis. Continuous variables will be expressed as either mean ± standard deviation (assuming normal distribution) or median (interquartile range) (non-normal distribution). For the primary outcome, Poisson regression or negative binomial regression will be used based on overdispersion tests (assuming Poisson or negative binomial distribution). For secondary outcomes: count data will use the same methods as the primary outcome; binary data will use logistic regression (assuming binomial distribution); continuous data will use repeated-measures analysis of variance (for normal distribution) or Friedman test (for non-normal distribution). Mauchly’s test will first be applied to assess sphericity for repeated measures. If the assumption is violated (*p* < 0.05), the Greenhouse–Geisser correction will be implemented. Pairwise comparisons within groups will use the Bonferroni method, between groups the LSD-*t* test (equal variances) or Tamhane’s T2 method (unequal variances). Categorical variables will be presented as frequency (%) and compared using the chi-square test (large samples) or Fisher’s exact test (small samples with <5 expected counts). Outliers will be identified using box plots (values beyond 1.5 × interquartile range), verified for data accuracy, and retained in the primary analysis; sensitivity analyses excluding outliers will be conducted. For all statistical tests, both *p*-values and 95% confidence intervals will be reported. A hierarchical testing strategy will be used for multiple comparisons: the primary outcome will be tested first; if significant, secondary outcomes will be tested with Bonferroni correction to control type I error, aligning with the outcome hierarchy. A *p*-value <0.05 is considered statistically significant.

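### The outlier-exclusion sensitivity analysis does not exempt exacerbation counts, so it would delete verified outcome data unequally by arm and bias the rate ratio, in a direction the plan leaves open

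*Protocol article*

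**What the plan says.** Section 2.9 (Statistical analysis) of the protocol article gives one general rule: "Outliers will be identified using box plots (values beyond 1.5 × interquartile range), verified for data accuracy", and then "retained in the primary analysis; sensitivity analyses excluding outliers will be conducted". It names no outcome to which the rule does or does not apply, and does not say whether the box plot is drawn on both arms together or on each arm separately. The same section analyses the primary outcome, the exacerbation count, by Poisson or negative binomial regression, and applies the same methods to secondary counts such as exacerbations leading to hospitalisation.

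Section 2.4 (Sample size) gives the planning rates: "the annual frequency of acute exacerbations in the control group was 1.08 episodes" and "the experimental group is expected to have a 40% reduction (28), i.e., 0.648 episodes". It states no dispersion. Section 2.7.1 defines the primary outcome as the total over 52 weeks, confirmed from diaries, patient reports and medical records.

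**The concern.** The 1.5 × IQR fence suits roughly symmetric continuous data. On a count with a mean near 1 the quartiles are 0 and 1 or 0 and 2, so the fence falls among values that a Poisson or negative binomial model fully expects. Values are verified before they are excluded, so what is removed is real outcome data and not error.

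The removal also selects on the post-randomisation outcome. If treatment works, the two arms have different upper tails, so the rule cuts them unequally and the remaining comparison is biased. A reader who takes this run as a test of robustness could think a true effect fragile, or larger than it is, purely because of the rule.

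**Working it through.** **Inputs.** Section 2.4: control rate 1.08; 40% reduction; α and power from "of the hypothesis test were set at 0.05 and 0.9"; 1:1 allocation; 359 evaluable and 424 randomised per arm. Assumptions: 52 weeks' exposure for everyone; two-sided α; negative binomial variance m + k·m², with k = 0 meaning Poisson; k from 0 to 3.2.

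**The plan's own figures.** 1.08 × 0.60 = 0.648 reproduces. For the sample size, n per arm = (1.960 + 1.282)² × (1/1.08 + 1/0.648 + 2k) / (ln 0.6)². With k = 0 this is about 99, not 359; with k = 3.22 it is 358.7. So 359 needs an input that is not stated. That does not show 359 to be wrong, but it makes k near 3.2 a sensible upper end for the range. 359/0.85 gives 423, then 424 per arm and 848 in total, as stated.

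**Pooled fence.** Averaging the two arms' distributions, P(0) is 0.43 to 0.67 and P(≤1) is 0.78 to 0.82 across the range of k. Hence Q1 = 0, Q3 = 1, and the fence is 1 + 1.5 × 1 = 2.5: every count of 3 or more is excluded. In 2,000 simulated trials of 424 per arm at each k, the fence was 2.5 in at least 99%.

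**Mean after exclusion.** m* = Σ x·p(x) / Σ p(x), summed over x ≤ 2. Poisson case:
- Control: p(0), p(1), p(2) = 0.3396, 0.3668, 0.1981. Retained 0.904, so 9.6% are deleted (about 41 of 424); m* = 0.763/0.904 = 0.843.
- BFYS: 0.5231, 0.3390, 0.1098. Retained 0.972, so 2.8% are deleted (about 12 of 424); m* = 0.559/0.972 = 0.575.
- Ratio: 0.575/0.843 = 0.68, against a true 0.60.

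**By-arm fences.** The control arm's Q3 is 2 while its P(≤1) is below 0.75: this probability is 0.706 at k = 0, 0.743 at k = 1.5 and 0.755 at k = 2. With Q3 = 2 the control fence is 2 + 1.5 × 2 = 5.0. The BFYS arm has P(≤1) of about 0.85, so its fence stays at 2.5.

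| k | Pooled: deleted, control / BFYS | Pooled: all events discarded | Pooled: ratio | By arm: fences, control / BFYS | By arm: deleted, control / BFYS | By arm: ratio |
|---|---|---|---|---|---|---|
| 0 | 9.6% / 2.8% | 24% | 0.68 | 5.0 / 2.5 | 0.1% / 2.8% | 0.53 |
| 0.5 | 12.7% / 4.8% | 37% | 0.73 | 5.0 / 2.5 | 0.9% / 4.8% | 0.49 |
| 1 | 14.0% / 6.1% | 46% | 0.77 | 5.0 / 2.5 | 2.0% / 6.1% | 0.47 |
| 1.5 | 14.5% / 6.9% | 53% | 0.79 | 5.0 / 2.5 | 2.9% / 6.9% | 0.46 |
| 2 | 14.7% / 7.5% | 58% | 0.82 | 2.5 / 2.5 | as pooled | 0.82 |
| 3.2 | 14.4% / 8.2% | 66% | 0.85 | 2.5 / 2.5 | as pooled | 0.85 |

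Events discarded = (control share × 1.08 + BFYS share × 0.648) / 1.728; at k = 0, (0.294 × 1.08 + 0.138 × 0.648) / 1.728 = 0.235.

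The switch near k = 2 is not sharp in samples. By arm, the simulated control fence was 5.0 in 81% of trials at k = 1. It was 2.5 in 59% and 5.0 in 38% at k = 2, and 2.5 in 92% at k = 3.22.

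**Precision, pooled fence.** With 359 per arm before exclusion and SE² = Σ v*/(m*²·n*), where v* and n* are the variance and number left in each arm, approximate power goes from 0.996 to 0.70 at k = 1 and from 0.90 to 0.19 at k = 3.22. At k = 0 it stays above 0.99.

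**Other event rates, same 40% reduction, pooled.** At a control rate of 1.3 with k up to 1 the fence is 5.0 and the ratio 0.60–0.67. At 1.5 with k up to 2 the fence is 5.0 and the ratio 0.61–0.75.

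**Hospitalised exacerbations.** No rate is given. If fewer than 25% of participants have one (assumption), Q1 = Q3 = 0, the fence is 0 and every participant with an event is excluded.

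**The case against.** The best reply is that this is a supplementary run, described in one general data-handling sentence of a condensed article. All values stay in the primary analysis, no decision hangs on the run, and scope and pooling could be settled in a statistical analysis plan that is not shown. Much of this stands: the primary estimate, its type I error and the testing hierarchy are untouched, and that limits the severity. What does not stand is that this is only missing detail. The article fixes the rule and exempts nothing, and pooled or by-arm use both give a biased result at the planning rates.

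Four stronger readings are tempting, and the documents do not support them:
- **That the rule necessarily removes more controls and shrinks the effect.** This holds for a pooled fence. By arm, with k up to about 1.5, more BFYS participants are removed and the effect is exaggerated.
- **That the cut is always at 3 exacerbations.** It is at the planning rates with a pooled fence; at higher rates it can move to 6 or more.
- **That the run would contradict a true benefit or breach intention-to-treat.** Every ratio above still favours BFYS, so the pooled result is attenuation with loss of power, and the intention-to-treat analysis keeps all randomised participants.
- **That those removed are the trial's target population.** The frequent exacerbator phenotype is defined by the year before entry, so every participant has it whatever the count on trial.

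**Conclusion.** The point holds as a defect of the sensitivity analysis only. Applied as written to the exacerbation count, the rule deletes verified outcomes unequally by arm. At 1.08 against 0.648 it moves a true ratio of 0.60 to 0.68–0.85 with a pooled box plot, or to 0.46–0.53 with by-arm box plots and k up to about 1.5. At k = 1 that one unstated choice separates 0.77 from 0.47 on the same data. The size rests on the planning rates, the assumed range of k and full 52-week exposure. At a higher event rate the pooled distortion can be small (0.61 at 1.5 per year under Poisson), but its direction is still towards 1. It should be changed; it does not threaten the primary result.

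**What to change.** In section 2.9, limit the outlier step to finding and correcting data errors, and state that count endpoints (exacerbations and exacerbations leading to hospitalisation) are exempt from exclusion. If a check on influential counts is wanted, keep every participant and use either robust (sandwich) standard errors or a count winsorised at a pre-specified cut-off set on blinded, pooled data. Nothing here shows harm for continuous outcomes, so a change of method there would be a preference only.

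The cost is one changed sentence and one sensitivity run replaced by another. The Trial status section schedules analysis to begin in March 2027, so the wording can be settled before then.

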#### Secondary outcomes

2.7.2

Secondary outcomes include the following indicators:

(1) Number of AECOPD episodes leading to hospitalization: Hospitalizations due to AECOPD should be promptly recorded in the study diary. The frequency should be recorded every 13 weeks during the study period.(2) Mortality: At the end of the study, the mortality of the two groups will be measured, including the AECOPD-related mortality and all-cause mortality.(3) Lung function: Tests will include forced vital capacity (FVC), forced expiratory volume in 1 second (FEV1), FEV1% predicted, and FEV1/FVC. Measurements will be conducted at baseline and every 13 weeks during the study period.(4) Clinical symptoms and signs scores: Assessments will cover cough, expectoration, wheezing, chest tightness, fatigue, cyanosis, etc. Each item will be scored on a 0–3 scale. Higher scores indicate worse disease status. Evaluations will be performed at baseline and every 13 weeks after the start of the trial.(5) Six-minute walking distance (6MWD): The total distance walked by patients on a flat surface within 6 min reflects exercise capacity. A greater distance indicates better exercise capacity (29). 6MWD will be measured at baseline and every 13 weeks during the study period.(6) Quality of life: The COPD assessment test (CAT) and 36-item short-form health survey (SF-36) are used to assess the quality of life of patients. A higher SF-36 score indicates better quality of life, while a higher CAT score indicates worse quality of life (30, 31). These questionnaires will be administered at baseline and every 13 weeks after trial initiation.

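### Holm's step-down would serve the secondary outcomes at least as well as the planned Bonferroni correction, at the same 0.05 family-wise bound

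*Protocol article*

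**What the plan says.** The multiplicity rule is in section 2.9 (Statistical analysis). It has two steps: "the primary outcome will be tested first", and then "if significant, secondary outcomes will be tested with Bonferroni correction to control type I error, aligning with the outcome hierarchy". The general threshold is that a p-"value <0.05 is considered statistically significant". For all tests, the section also promises that p-values and "95% confidence intervals will be reported"; it does not say that these intervals are adjusted for multiplicity.

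The family size is not given. Section 2.7.2 has six numbered entries, but several contain more than one variable. Mortality is reported "including the AECOPD-related mortality and all-cause mortality". For lung function, "Tests will include forced vital capacity (FVC), forced expiratory volume in 1 second (FEV1), FEV1% predicted, and FEV1/FVC". Quality of life uses both CAT and SF-36.

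Section 2.1 expects lung function, exercise capacity, symptoms and quality of life to improve. The Discussion adds hospitalisations for exacerbation. Neither place predicts a mortality benefit.

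**The concern.** Plain Bonferroni holds each secondary outcome to 0.05/m however many of the others have already been rejected. Holm relaxes the threshold step by step and keeps the same guarantee. It needs no assumption that Bonferroni does not also need, and it can be computed from the p-values already planned.

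If the drug works broadly, as the sponsor expects, some true secondary benefits would be reported as not significant although the same data support them at the same guaranteed error level. The primary conclusion is not affected.

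**Working it through.** **No plan figure to reproduce.** The article gives no power, effect size, standard deviation or correlation for any secondary outcome. The sample size in section 2.4 concerns the primary outcome only and does not bear on this point.

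**Inputs from the article.** Level 0.05, taken as two-sided because sidedness is not stated. Family size m is 6 (numbered entries) or 11 (1 hospitalisation count + 2 mortality + 4 lung function + 1 symptom score + 1 walking distance + 2 quality-of-life scales = 11).

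**Assumptions.** Unadjusted power per real effect 80% or 90%; equal correlation of 0.3 or 0.6 between test statistics; one test per outcome. The number of real effects is varied. The sponsor's expectation covers everything except mortality: 5 of 6 entries, or 11 − 2 = 9 of 11 variables.

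**Thresholds.**
- Bonferroni: 0.05/6 = 0.00833 or 0.05/11 = 0.00455 for every test.
- Holm, m = 6, smallest p-value first: 0.00833, 0.0100, 0.0125, 0.0167, 0.025, 0.05. For m = 11 it runs from 0.00455 to 0.05 in the same way. Testing stops at the first failure.

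Every Holm threshold is at least 0.05/m, so Holm rejects whatever Bonferroni rejects.

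**Same bound.** Suppose m₀ nulls are true. When Holm first rejects a true null, at most m − m₀ hypotheses have been rejected before it, so its threshold is at most 0.05/m₀. The chance that any of m₀ true nulls has a p-value that small is at most m₀ × 0.05/m₀ = 0.05, whatever the dependence.

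**Bonferroni power per real effect.** Power = Φ(z₀.₀₂₅ + z_power − z at 0.025/m), neglecting the opposite tail.
- m = 11: Φ(2.802 − 2.838) = 48.6% from 80%; Φ(3.242 − 2.838) = 65.7% from 90%.
- m = 6: Φ(2.802 − 2.638) = 56.5% from 80%; Φ(3.242 − 2.638) = 72.7% from 90%.

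**Holm against Bonferroni.** These are simulated correlated two-sided z-tests, with both methods applied to the same data. The figures are the average share of true effects declared.

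| Family, real effects | Unadjusted power | Bonferroni | Holm |
|---|---|---|---|
| 11, 9 real | 80% | 48–49% | 55–56% |
| 11, 9 real | 90% | 66% | 73–74% |
| 6, 5 real | 80% | 56–57% | 63–64% |
| 6, 5 real | 90% | 73% | 79–80% |
| 11, 5 real, or 6, 3 real | 80–90% | 49–73% | about 3 points higher |
| 6 or 11, 1 real | 80–90% | 48–73% | 0.1 point higher or less |

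With 9 of 11 real, Holm declared at least one additional outcome in 40–51% of simulated trials. It never lost a rejection.

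**What does not change.** The smallest p-value faces 0.05/m under both methods, so the chance of at least one secondary success is identical.

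**Actual family-wise error.** With all nulls true it is identical (m = 6, correlation 0: 0.049 for both). With some effects real, Holm uses more of the allowance. With 9 of 11 real it is about 0.009 for Bonferroni and 0.023–0.029 for Holm. With 3 of 6 real, 80% power and correlation 0, it is 0.024 and 0.036. It stays within 0.05 throughout.

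**The case against.** The strongest reply is that nothing is wrong. Bonferroni after a primary gatekeeper is a valid, common and conservative choice that controls type I error as the article says. That stands.

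The size of the gain also rests on inputs the article does not supply. Broad benefit is the sponsor's expectation, not a power calculation, and with one real effect the gain vanishes. That stands too, and is why a range is given. The statistical analysis plan is not shown and may define the family more closely; the phrase about aligning with the outcome hierarchy is unexplained. Plain single-step testing is therefore the natural reading, not a certainty.

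Bonferroni has one real advantage: matching simultaneous intervals at level 1 − 0.05/m. A plan that wanted them would have a reason to keep it. Section 2.9, however, promises only 95% intervals and says nothing of adjustment, so the advantage is available but not claimed.

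A reader might count every visit as a separate member of the family and reach 35 tests. The article does not support this. Section 2.9 gives continuous outcomes a repeated-measures analysis and assigns between-group pairwise comparisons to LSD-t or Tamhane's T2, not to the Bonferroni step.

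**Conclusion.** The point holds as an efficiency improvement. Under 80–90% unadjusted power and correlation 0.3–0.6, Holm adds about 7–8 points to the share of true effects declared if nearly all are real, about 3 if half are, and practically none if only one is. That Holm is never less powerful does not depend on these assumptions; the size of the gain does.

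Three stronger readings are tempting and should be resisted.
- That Holm wins on every outcome: an outcome gains only when others are also rejected.
- That it has the same type I error: the bound is the same, but the actual error is equal only when all nulls are true.
- That Bonferroni buys nothing: it offers simple simultaneous intervals, even if this plan does not say it will use them.

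The passage contains no contradiction or error on this point.

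**What to change.** In section 2.9, and in the statistical analysis plan if it repeats the rule, replace *with Bonferroni correction* by *with the Holm step-down procedure*, and keep the secondary family and analyses as planned. Restricting repeated measures to a single week-52 contrast would be a separate decision, which this change does not need.

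The cost is one sentence, with no extra patients, visits or data. Two small downsides should be accepted knowingly: Holm has no equally simple simultaneous confidence intervals, and it uses more of the permitted 0.05 when some effects are real. The article's Trial status section schedules analysis to begin on March 1, 2027, and recruitment was still under way at its last count, so the change can be made before the results are known.

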#### Quality control

2.8.2

In order to ensure the quality of this trial, we will establish a quality control committee and a data monitoring committee (DMC). DMC comprises 3 independent experts (1 statistician, 1 pulmonologist, and 1 TCM specialist) with no affiliations to the sponsors or research centers. The committee conducts monthly evaluations on the following aspects: protocol adherence (consistency of interventions, compliance with inclusion and exclusion criteria), data accuracy (verification of 10% of CRFs against original documents), and safety profile (analysis of adverse events). Researchers will comply with the guidelines of good clinical practice (GCP). Quality control experts will conduct monthly quality control assessments to ensure the quality of the study. Additionally, all researchers will receive standardized training on the study protocol. Last but not least, enhancing participants’ compliance is another important measure for quality control. Strategies to improve compliance include monthly telephone follow-ups with participants, quarterly home visits for participants, provision of health education materials, and offering appropriate subsidies, etc.

Additionally, an interim analysis will be conducted by the DMC when 50% of follow-up data are accumulated, assessing efficacy, safety, and futility using the O’Brien-Fleming alpha spending function to control type I error. The DMC will recommend continuation, early termination, or modification based on results. Blinding effectiveness will be evaluated post-trial via questionnaires for investigators and participants to guess group allocation. Correct guess proportions will be compared with 50% (random chance) using the chi-square test; non-significant deviation indicates successful blinding.

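### Section 2.9 sets significance at p<0.05 without exempting the final primary test, although section 2.8.2 spends part of that alpha at an efficacy interim

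*Protocol article*

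**What the plan says.** Three places in the protocol article bear on the primary test.

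- **Section 2.4 (Sample size)** fixes the design error rates: alpha and power "of the hypothesis test were set at 0.05 and 0.9". It does not say whether alpha is one-sided or two-sided.
- **Section 2.8.2 (Quality control)** states that "an interim analysis will be conducted by the DMC when 50% of follow-up data are accumulated". The look covers efficacy, safety and futility, and an O'Brien-Fleming spending function is named as the means of type I error control. Early stopping is possible: "The DMC will recommend continuation, early termination, or modification based on results".
- **Section 2.9 (Statistical analysis)** sets a hierarchy in which the primary outcome comes first and, if it is significant, the secondary outcomes follow with a Bonferroni correction. The closing criterion is "value <0.05 is considered statistically significant". The section does not refer to the interim analysis and makes no exception for the primary outcome.

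**The concern.** Alpha spent at an efficacy look is not available again at the end. If 2.8.2 governs, the nominal level of the final primary test must be below 0.05. If the 2.9 criterion governs, the error control promised in 2.8.2 is not fully delivered. The two statements cannot both define significance for the same test.

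A narrow band of final p-values is at stake, from the remaining boundary up to 0.05. A result in that band would be a success under one section and a failure under the other. Because the primary result opens the secondary tests, the same band also decides whether any secondary outcome may be claimed.

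**Working it through.** **Inputs from the protocol.** Overall alpha 0.05 (2.4); one interim look at 50% of follow-up data with O'Brien-Fleming spending (2.8.2); final criterion p<0.05 (2.9). The protocol prints no interim or final boundary, so there is no plan figure to reproduce on this point.

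**Assumptions.** Two-sided alpha, split as 0.025 per side; first, 50% of follow-up taken as information fraction t = 0.5.

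**Step 1: alpha spent at the interim.** The Lan-DeMets O'Brien-Fleming-type function, per side, is 2 − 2Φ(z/√t), with z the upper 0.0125 point.
- z = 2.2414, and 2.2414/√0.5 = 3.170.
- Two-sided alpha spent = 2 × (2 − 2Φ(3.170)) = 0.00305, so the interim boundary is |Z1| ≥ 2.963.

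**Step 2: level left for the final test.** Z1 and Z2 are bivariate normal with correlation √0.5 = 0.707. Solve P(|Z1| ≥ 2.963 or |Z2| ≥ c) = 0.05.
- c = 1.969, a two-sided p of 0.0490.

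**Step 3: error rate if 0.05 is used at the end.** P(|Z1| ≥ 2.963 or |Z2| ≥ 1.960) = 0.0510.

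**Step 4: is t = 0.5 at half of the follow-up?** For an overdispersed count, a patient with rate λ followed for time f contributes information proportional to λf/(1 + kλf). Early follow-up therefore counts for more when the dispersion k is above zero.
- Rates: "the annual frequency of acute exacerbations in the control group was 1.08 episodes" and "the experimental group is expected to have a 40% reduction", so 1.08 and 0.648 per year.
- Accrual: assumed uniform over the 18 months from July 2024 to December 2025 (Trial status), with one year of follow-up each. Half of the person-time is then reached at 1.25 years: (0.25 × 1 + 1 × 0.5)/1.5 = 0.5.
- Dispersion: the protocol gives none. I used k = 1 as an illustration. I also used k = 3.2, the value at which a two-sided negative binomial formula at 90% power returns the 359 per group of section 2.4; a plain Poisson formula gives only 98 to 100.
- Result: t = 0.50 at k = 0, 0.57 at k = 1, 0.64 at k = 3.2.

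**Step 5: repeat steps 1 to 3.**

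| t | Interim p | Final p left | Overall error with 0.05 at the end |
|---|---|---|---|
| 0.50 | 0.0031 | 0.0490 | 5.10% |
| 0.57 | 0.0060 | 0.0481 | 5.19% |
| 0.64 | 0.0102 | 0.0468 | 5.30% |

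**Sensitivity to the boundary version, at t = 0.5.**
- Classical O'Brien-Fleming: final level 0.0480, overall error 5.20%.
- Spending 0.05 without splitting it by side: 0.0478 and 5.22%.
- One-sided alpha of 0.05: 0.0482 and 5.17%.

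In every version the final level is below 0.05.

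**Power.** At t = 0.5 and fixed sample size, using the correct final boundary lowers power from 90.0% to 89.9%. The sample size inflation factor is 1.003.

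**The case against.** The strongest defence is that 2.8.2 already settles the matter. A spending function fixes the final level as well as the interim one, so a trial that follows 2.8.2 will use about 0.049 or less. On this view the 0.05 in 2.9 is a general convention closing a paragraph about all outcomes, or a restatement of the overall alpha in 2.4. It cannot be literal for every test, since the sentence before it puts the secondary outcomes under Bonferroni. Exact boundaries usually sit in an analysis plan, which is not shown.

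Much of this stands. The intent to control type I error is clear, and the absence of printed boundaries is no fault. But the point does not rest on a missing boundary; it rests on a threshold that is stated. Section 2.9 modifies 0.05 for the secondary outcomes and makes no such modification for the primary outcome. It words 0.05 as a criterion for a p-value, while the overall alpha is set separately in 2.4. An analysis plan with the remaining boundary would depart from 2.9, and one repeating 0.05 would depart from 2.8.2.

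A reader might also infer three stronger things that the protocol does not support:
- **That 0.05 applies at both looks.** Section 2.8.2 rules this out by naming O'Brien-Fleming spending for the interim.
- **That the spending function is meant to serve as the futility rule.** Its stated purpose is type I error control, and a futility rule is properly left to a committee charter or analysis plan.
- **That the committee's power to recommend modification means redesign on the unblinded effect.** The protocol does not say so, and limits on modification also belong in a charter.

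**Conclusion.** The inconsistency is real and minor. Taken literally, 2.9 tests the final primary hypothesis above the level left by 2.8.2. The excess in overall type I error is about 0.1 percentage point at information 0.5 and about 0.2 to 0.3 at 0.57 to 0.64. The larger figures rest on assumed dispersion and uniform accrual. All the table figures assume a two-sided alpha split equally by side.

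A reader might conclude that the trial's type I error will exceed 5%. The documents do not support that as settled fact: it follows only if the analysts apply 2.9 and disregard 2.8.2. What is established is that the protocol gives two incompatible criteria for its main test and for the gate to the secondary outcomes.

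**What to change.** Replace the closing criterion in 2.9, for the primary outcome, with wording such as:

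> The final test of the primary outcome is significant only if it crosses the final boundary left by the O'Brien-Fleming spending function, computed at the information fraction actually observed at the interim (two-sided p<0.049 if that fraction is 0.5). Secondary outcomes are tested only after that boundary is crossed. p<0.05 is not the criterion for the final primary test.

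The 0.049 should stay conditional on a fraction of 0.5, since a later look in information lowers it. The wording also settles that the test is two-sided, which 2.4 leaves open. No change to the futility or modification text is needed for this point.

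The cost is one short insertion, a slightly stricter final threshold and about 0.1 percentage point of power at information 0.5. Data collection is expected to finish in December 2026 and analysis to start in March 2027 (Trial status), so the clarification can be made before the final analysis.
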